#### Household, CHWs and health facility surveys

The primary outcome in both sites will be collected using an end-line household survey administered to the child’s primary carer. Data will be collected on illness prevalence, proportion of children who have received appropriate treatment and on household socio-economic status. Secondary outcomes, such as CHW performance, will be assessed in a sample of CHWs using a structured questionnaire with pre-tested case scenarios and knowledge questions administered by a trained research assistant. A motivation tool has been developed and validated to establish a composite index of CHW motivation. A health facility questionnaire will be used to collect data from health facility staff/supervisors on CHW supervision, support and health system costs.

The quantitative survey questionnaires will be adopted from the tools used for the baseline survey. These were developed in an iterative process: i) with the team of researchers in London and Kampala/Mozambique, ii) with potential field supervisors, and finally, iii) with trainees of the data collector training. Both the field supervisors and data collectors will visit local homes under supervision of a researcher to practice and test the questions and make revisions. All questionnaires will be written in English and translated into the local languages (Runyoro, Luo and Luganda for Uganda and Portuguese for Mozambique), and the accuracy of the translation will be checked by back translation into English. Key illness terminologies and other sensitive expressions will be translated into the native languages during the training and provided to the research assistants on a hard copy which guided them during the interview. Field editing will be done for consistency and completeness and after correction, data will be double-entered by trained data entry clerks into a SQL data management system capable of consistency, range, inter-database checks and audit trails.

#### Intention-to-treat analyses

All analyses will be intention-to-treat, and will account for the cluster-randomised design. Initial crude analyses will be based on summary measures for each outcome in each cluster and t-tests will be used to compare each intervention arm with the control arm. Multivariate random-effects models, which allow for cluster-specific constant amounts and work well for normally distributed outcomes and Poisson outcomes, will be used to assess the effect of the intervention on retention, motivation and coverage of appropriate treatment; adjustments will be made to account for clustering and any imbalances found between groups at baseline.. Random effects logistic regression models can be computationally demanding, and can fail to converge; if this is the case, generalized estimating equations (GEE) will be used instead if the random effects are found to be unreliable. The GEE approach modifies both parameter estimates and standard errors to allow for clustering and are appropriate where the clusters themselves are of no intrinsic interest. According to the analysis approach proposed [27], random effects models, whatever the outcome, will be used, only reverting to GEE where these do not converge.

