### Randomisation

Restricted randomisation was performed to minimise the difference between the intervention and control arms for key indicators of the average proportion of children appropriately treated for fever, diarrhoea, and pneumonia (FDP); VHT motivation (mean); and the mean (log10) cost of treatment for children with FDP [19]. The randomisation of clusters to the three arms was restricted to those randomisation schemes where there were minimal between-arm differences for these five key parameters but still allowed adequate numbers of randomisation schemes, as too few schemes could elicit selection bias [20].

In Mozambique, appropriate treatment for childhood FDP could not be measured reliably at baseline due to a delay in the roll-out of the APE kits containing iCCM medicines. Attempts to seek care from an APE or a public facility were chosen as proxy markers for overall appropriate treatment, as these showed the strongest correlation with appropriate treatment. This was based on an assessment of the relationship between appropriate treatment with these and other candidate variables using parallel data from the Uganda baseline survey (where appropriate treatment was measured), and by assessment of the cluster averages and variances for several care seeking variables from the Mozambique dataset itself.

In Uganda, out of 500,000 random allocations of 39 clusters to three arms, 13,683 of the allocations fit all criteria. After applying a further filter to ensure that all districts had at least one sub-county in the mHealth intervention arm, and that at least the larger districts had a control arm, a final scheme was picked from the resulting sub-sample of 1,791 allocation schemes. In this scheme, all districts had at least one sub-county in the control arm and one in the mHealth intervention arm, and five out of eight districts also had at least one sub-county in the participatory community engagement arm (Figure 5).

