**Interventions and control arm clusters in Uganda.**

Within Mozambique, there were 924 possible unique ways to sort 12 districts into two groups. In total, 84 schemes from these potential 924 met the all restriction criteria. A scheme was picked at random from the final 84 schemes, and was thus the final chosen scheme for the Mozambique study (Figure 6). In both sites, the selected schemes had no more than a 5% (proportions) or a 0.5 (scores/counts) difference between arms for any parameter. Sorting of clusters and random selection of schemes were carried out in Stata v12.1 (StataCorp, Texas USA).

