### Sample size

The sample size calculations, which are based on a cluster RCT with 13 and 6 clusters per arm in Uganda and Mozambique, respectively, are based on the main evaluation outcome: the percentage of children receiving appropriate treatment during illness episodes for each of pneumonia, diarrhoea and fever. This is also the outcome that requires the largest samples, as not all children surveyed will have had a recent illness episode. Inter-cluster coefficients of variation, baseline appropriate treatment rates, and prevalences of illness were calculated from data collected during the baseline surveys in each site and used in the sample size calculations (assuming a 5% significance level).

The calculation was based on the formula for comparison of proportions, adjusted for cluster effects stated in equation 7.7 of Hayes and Moulton [21], that is, where k is the between cluster coefficient of variation:$$ C = 1 + \left(\mathrm{z}\upalpha /2 + \mathrm{z}\upbeta \right)2\left(\ \left(\uppi 0\left(1\ \hbox{--}\ \uppi 0\right)/\mathrm{m} + \uppi 1\left(1\ \hbox{--}\ \uppi 1\right)/\mathrm{m} + \mathrm{k}2\left(\ \uppi 02 + \uppi 12\right)\right)\ /\left(\uppi 0\ \hbox{--}\ \uppi 1\right)2\ \right) $$

The number of sick children required/cluster was determined by varying this number in the formula for the number of clusters until the number of clusters/arm equals 13 and 6, respectively [21]. Thus, sampling 155 children per cluster in Uganda would yield enough sick children to have 90% power to detect a 15% difference in the appropriate treatment of pneumonia and fever and a 20% difference in diarrhoea between arms. Sampling 390 children per cluster in Mozambique would yield enough sick children to have 90% power to detect 20% and 25% differences in appropriate treatment of fever and pneumonia respectively, and 80% power to detect a 25% difference in appropriate treatment of diarrhoea between arms.

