### Impact evaluation

The primary outcome is the change in carer reported appropriate treatment for fever, diarrhoea and pneumonia in children in households receiving the intervention(s) compared to those in areas with routine iCCM (‘control’ households). A proportion of children will have had two or more conditions simultaneously. We intend to group all conditions and assess the ‘use of appropriate drugs for this episode of illness for all illness episodes by intervention arm. Additionally, the effect of the interventions on appropriate treatment for each of the three conditions individually will be established as a way of understanding the pathways through which the interventions worked. The main comparison for effect will be obtained from the measured difference between interventions and control arms at end-line. Baseline characteristics were used to perform restricted randomisation to minimise the difference between the intervention and control arms on key indicators.

Secondary outcomes include a number of performance, retention, motivation, access and cost-effectiveness outcomes:Mean motivation score (motivation outcome)% CHWs staying in post after 1 year of implementation (retention outcome)% monthly reports complete and submitted on time (performance outcome)% CHWs with medicine stock-out <1 week each quarter (performance outcome)% caregivers with sick child in the last 2 weeks who accessed iCCM treatment (coverage outcome)% caregivers willing to use CHWs (access outcome)% of start-up costs compared to recurring costs of the intervention packages (cost outcome)Cost per CHW trained (cost outcome)% of start-up costs compared to recurring costs of the intervention packages (cost outcome)Cost per child who receives appropriate treatment for each of diarrhoea, pneumonia and fever (cost-effectiveness outcome)Cost per episode of illness treated correctly (cost-effectiveness outcome)Cost- per life year gained (LYG) and DALY averted (cost-effectiveness outcome)

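### Allocation was tightly restricted on baseline cluster variables, but adjusting only for imbalances that appear tends to omit those variables, so tests are conservative and intervals too wide

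*Protocol article*

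**What the plan says.** **Allocation (Randomisation section).** Schemes were "restricted to those randomisation schemes where there were minimal between-arm differences for these five key parameters". In Uganda the five are baseline appropriate treatment for fever, diarrhoea and pneumonia, mean motivation, and mean log10 treatment cost. In Mozambique, appropriate treatment could not be measured reliably at baseline, so seeking care from a community health worker or a public facility stood in for it. These proxies were chosen for their correlation with appropriate treatment. The schemes finally used had "no more than a 5% (proportions) or a 0.5 (scores/counts) difference between arms for any parameter".

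**Analysis (Intention-to-treat analyses section).** A crude cluster-level t-test comes first, then random-effects models, with GEE as the fallback. On covariates the article says "adjustments will be made to account for clustering and any imbalances found between groups at baseline". It does not say that the restriction variables enter the model, and it names no permutation test over the accepted schemes.

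**Comparison (Impact evaluation section).** "The main comparison for effect will be obtained from the measured difference between interventions and control arms at end-line".

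**The concern.** The design and the adjustment rule pull against each other. The investigators chose the restriction variables because they expected them to predict the outcome, then forced the arms to agree on them. A rule that admits a covariate only when the arms differ on it will seldom admit these, and will pick up other variables that happen to differ.

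Restriction on a prognostic variable reduces the true sampling variance of the arm difference. An analysis without that variable estimates its standard error as if allocation had been unrestricted. The standard error is then too large, the actual type I error falls below 5%, and part of the precision that the restriction gained is not used in the inference. This matters most in Mozambique, with six clusters per arm.

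**Working it through.** **Inputs from the article**
- Clusters: "based on a cluster RCT with 13 and 6 clusters per arm in Uganda and Mozambique, respectively".
- Level: "assuming a 5% significance level", two-sided, since the printed formula uses z at alpha/2.
- Mozambique: 84 accepted schemes of 924. Uganda: 13,683 of 500,000, then 1,791 after the district filter.

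**Article's figure reproduced.** C(12,6) = 924, as stated. Accepted shares: 84/924 = 9.1%; 13,683/500,000 = 2.7%; 1,791/500,000 = 0.36%. The restriction was tight.

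**Assumption.** The article gives no correlation r between the baseline variable and the end-line cluster outcome, nor R2 (the share of between-cluster outcome variance explained by several such variables). Both are varied.

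**Approximation by hand.** If restriction holds the baseline difference near zero, the true SD of the arm difference is about √(1 - r²) times what the unadjusted standard error assumes. The actual type I error is then about P(|t| > t_crit/√(1 - r²)). For Mozambique, with 10 df, t_crit = 2.228:
- r = 0.3: 2.228/0.954 = 2.34, about 4.2%
- r = 0.5: 2.228/0.866 = 2.57, about 2.8%
- r = 0.7: 2.228/0.714 = 3.12, about 1.1%

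**Simulation, Mozambique, one covariate** (best 84 of 924 schemes by baseline difference; effect set for 80% power under unrestricted allocation; cluster-level t-test against cluster-level regression):

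| r | Unadjusted type I error | Change in power from adjusting |
|---|---|---|
| 0 | about 5% | about -1 point |
| 0.3 | about 4.5% | about +2 |
| 0.5 | about 2.6% | about +7 |
| 0.7 | about 0.9% | about +13 |

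Adjusted type I error stays near 5% throughout. A repeat with 20,000 runs per row gave 5.0%, 4.2%, 2.5% and 1.0%, and the same rounded power changes.

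**Simulation, several covariates** (2,500 runs per cell; an imbalance counted as found at baseline p < 0.10, an assumption). The restriction variables never met that trigger, so the article's rule gave the unadjusted test.

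| Setting | R2 | Type I error, article's rule | Power, article's rule | Power, adjusted |
|---|---|---|---|---|
| Mozambique, 2 covariates | 0 | 4.9% | 85% | 82% |
| | 0.25 | 2.8% | 87% | 92% |
| | 0.5 | 0.8% | 88% | 98% |
| Mozambique, 4 covariates | 0 | 5.1% | 84% | 74% |
| | 0.25 | 3.1% | 87% | 85% |
| | 0.5 | 1.6% | 89% | 95% |
| Uganda, 5 covariates | 0 | 4.8% | 91% | 88% |
| | 0.25 | 3.0% | 92% | 94% |
| | 0.5 | 2.0% | 94% | 99% |

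Type I error with adjustment was 4.4 to 5.8% in all scenarios run (R2 up to 0.75).

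**Interval width.** At R2 = 0.5 in Mozambique the unadjusted analysis assumes an SD of √(2/6) = 0.577 (in between-cluster SD units), while the true SD is 0.42 to 0.45. The ratio is 0.577/0.45 = 1.28 to 0.577/0.42 = 1.37. In Uganda it is √(2/13) = 0.392 against 0.32, or 1.23.

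**Permutation test over the 84 schemes.** It keeps its level (4.6 to 5.1%). With two covariates its power is 77% at R2 = 0, 85% at 0.25 and 93% at 0.5, so it costs more than covariate adjustment when the variables are weak.

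**The case against.** **The error is on the safe side, and no planned power is missed.** This stands. A reader might infer false-positive inflation or a shortfall against the stated power. Neither follows: type I error falls, and the sample size formula takes no credit for restriction or covariates. The claim that "sampling 155 children per cluster in Uganda would yield enough sick children to have 90% power to detect a 15% difference" is untouched. What goes unused is a gain the plan never counted on.

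**The correlation may be low.** This stands as a limit on size. Uganda's baseline began about three months after 31 January 2011 and its end-line survey was in March to May 2014, about three years later. Mozambique has only proxies. Baseline cluster rates are also noisy. If the 6,501 Ugandan children are spread over 39 clusters, there are about 167 per cluster, or about 78 with fever (47%), 40 with pneumonia (24%) and 18 with diarrhoea (11%). With k = 0.15 and an assumed rate of 0.4, reliability is 0.0036/(0.0036 + 0.24/m), about 0.54, 0.38 and 0.22. At r = 0.3 the gain is only about 2 points.

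**A covariate list may sit in an analysis plan that is not shown.** This stands in part. Baseline also preceded randomisation, so imbalance can be judged without end-line data. But the article states a selection rule, and it is that rule, not missing detail, that works against the design.

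**Two further readings are not supported.** The Impact evaluation section says "The primary outcome is the change in carer reported appropriate treatment for fever, diarrhoea and pneumonia", from which a reader might infer a planned change from baseline that Mozambique could not compute. The sentence goes on to contrast intervention with control households, and the same paragraph fixes the comparison at end-line, so this is at most loose wording. A reader might also take the 0.5 limit as allowing a 10^0.5 = 3.2-fold difference in cost. The article states that limit for scores and counts and does not say it was applied to log10 cost. So large a gap would itself count as an imbalance and be adjusted for.

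**Conclusion.** The point holds in a limited form. The adjustment rule tends to omit the variables used to restrict allocation, so the standard error, p-value and interval do not reflect the precision the restriction gave to the estimate. The test is conservative and the intervals are too wide.

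The consequence runs from nothing at r = 0 to a type I error of about 0.9% and about 13 points of unused power at r = 0.7 (Mozambique, one covariate). The article does not show where in that range the trial lies. The figures rest on assumed correlations, cluster-level regressions in place of the random-effects models, and schemes ranked on closeness of the simulated baseline variables, since the actual criteria are given only in outline.

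This is a worthwhile correction to the analysis rule. It does not threaten the validity of a positive finding.

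**What to change.** Replace the imbalance-triggered rule with fixed adjustment, whatever the observed balance:
- **Uganda, primary outcome:** the cluster-level baseline value of the same outcome.
- **Mozambique, primary outcome:** one, at most two, of the care-seeking proxies used in the restriction.
- **Motivation and cost outcomes:** their own baseline cluster mean.
- **Alternative:** a permutation test over the accepted schemes.

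Reword the primary outcome as the end-line difference between arms.

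**Cost.** The baseline data exist. Adjustment uses one or two degrees of freedom and loses about 1 to 3 points of power in Mozambique if the covariates are not prognostic. Four covariates there would lose about 10 points (84% to 74%), hence the cap. Because Uganda's end-line data had already been collected, the change needs a written justification and should be fixed and dated before the arms are compared.

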#### Record review

During the project cycle, CHW record books will be reviewed to estimate the proportion of children classified with diarrhoea, malaria and pneumonia; the mRDT positivity rate, and frequency and outcome of referral. Drug stock cards will be reviewed to estimate drug stock-outs. Supervisor log books will be reviewed for frequency and content of supervision visits, and reports from district and health facility staff will be reviewed for CHW retention. Health facility records will be reviewed for patient load for health system costs. To estimate costs of CHW activities, the results of the process evaluation interviews described below will be combined with data collection from financial and activity reporting.

### Process evaluation and intervention monitoring

Process evaluation (PE), which started approximately 10 months after implementation of the interventions (January to February 2014 in Uganda and April to May 2014 in Mozambique), aims to identify lessons learned, successes and challenges and to crystallise best practices using key informant interviews with CHWs and their health facility supervisors. In Uganda, 24 VHTs and eight supervisors in the mHealth intervention, and 24 VHTs and eight supervisors in the participatory community engagement intervention in the districts of Buliisa, Hoima, Kyegegwa and Masindi were interviewed using predesigned topic guides. In Mozambique, 33 semi-structured key informant interviews with 24 APEs and nine supervisors were conducted in the districts of Inharrime, Morrumbene and Inhassoro of Inhambane Province. The qualitative most significant change methodology [28] was applied during the process evaluation as a way of monitoring changes observed as a result of the iCCM programme, and the interventions implemented, to document success stories from community members, CHWs and health workers. Specifically the process evaluation explored:whether the interventions were delivered as designed and taken up and utilised as intended.which the context-based factors had an impact on aspects of work motivation and satisfaction and the existing approaches to measuring motivation, instruments that could be adapted to the specific case of CHWs, best practices and new methods.whether the interventions influenced motivation, retention, performance and/or other factors.whether increased motivation impacted on performance and retention, and whether this lead to children receiving more appropriate treatment.how the programme was implemented, how the programme operated, the services it delivered, and the functions it carried out.

### Cost and cost-effectiveness evaluation

The cost and cost-effectiveness analyses will take a societal perspective, assessing the economic impact for all parties affected by the interventions.

#### Intervention costs

The costs of the intervention packages will be estimated both from a financial and economic perspective. Costs will include direct project expenditure incurred by the implementing partner, the costs borne by the MoH at the national and local level during the implementation phase, the value of the work time contributed by the volunteering CHWs in Uganda, and any non-reimbursed out-of-pocket costs incurred by the CHWs in relation to their work. In order to allow generalisability of the findings to other contexts, cost will be categorised by principal inputs and activities, with quantities and values collected separately as far as possible.

#### Household and community costs

Direct (out-of-pocket) costs as well as indirect costs (value of lost production) for households in relation to care and treatment-seeking will be measured at the end of the intervention trials across trial arms. Direct costs will include transport costs, out of pocket payments to service providers, and any money spent on items complementary to treatment. Indirect costs will focus on the time spent caring for the sick child and seeking care. Costs will be broken down by socioeconomic status.

#### Health facility costs

It is likely that resource use in local health facilities will be affected by the introduction of a new level of healthcare worker; due to changes in the numbers of children seeking care at the health centres, of severe cases seen due to early treatment in the community, and of cases referred. The unit costs of treating the illnesses included in the iCCM package at different facility levels will be estimated, including staff time, drugs, diagnostics and other consumables and the use of equipment and facilities. The costs per episode of care in different facilities will be brought together with health seeking behaviour information from the household survey to assess the net difference in resources use.

#### Cost-effectiveness analysis

The cost-effectiveness analysis will assess the incremental cost and outcomes of the two intervention and control arms in Uganda, and between the intervention arm and control arm in Mozambique. Incremental costs will be derived from the cost analyses above, combining unit costs with data on service provision/ utilisation from the trial surveys in each arm. Outcome measures will be based in the principal outcome measure of the intervention trial, the incremental difference in the number of sick children appropriately treated during the trial period. This outcome will then be converted into life-years gained (LYGs) and disability- adjusted life years (DALYs) averted using standard methods.

